## Abstract

**Background:**

Maternal overweight, infant feeding and early growth velocity are risk factors for obesity later in life. The first one thousand days are a window of opportunity to program health and disease. Exclusive breastfeeding may protect against obesity; however, it is not consistently practiced. Obesity rates have been increasing worldwide. Overweight or obese women have lower rates of breastfeeding and face mechanical, psychological and biological difficulties. Breastfeeding counselling is a successful strategy to support breastfeeding in normal weight women; but there is a lack of evidence on its effectiveness in overweight women. Our purpose is to evaluate a new approach to exclusive breastfeeding counselling based on Carl Rogers’ Centred-Client Theory in overweight women, and to examine effects on breastfeeding prevalence, infant growth velocity and maternal postpartum weight loss.

**Methods:**

A two-arm simple randomized controlled trial will be conducted in overweight and obese women recruited in a Baby Friendly Hospital in Bogotá, Colombia. The intervention is exclusive breastfeeding counselling based on Rogers’ theory but adapted for overweight women; it will be performed during the last month of pregnancy, 24 h after delivery and during early infancy (1 and 3 months postpartum). The primary outcomes will be exclusive breastfeeding prevalence, infant growth velocity and maternal weight loss from birth up to 4 months after delivery; and the secondary outcomes will be prolactin and macronutrient levels in breast milk and serum prolactin levels. Intention to treat analysis will be performed to estimate the effect of the new counselling approach compared to standard management on the prevalence of exclusive breastfeeding, infant growth velocity and maternal weight loss.

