## Background

In 2016, the World Health Organization (WHO) reported a worldwide prevalence of overweight (body mass index [BMI] higher than 25 kg/m^2^) and obesity (BMI > 30 kg/m^2^) of 40 and 15% respectively in women aged ≥18 years, with a global projection of 70 million overweight children aged under five years by 2025 [1], perpetuating the intergenerational transmission of obesity. In Colombia in 2015, the Instituto Colombiano de Bienestar Familiar (ICBF) reported a prevalence of overweight in the adult population of 37%, of which 22% were obese woman, and a prevalence of 6.3% of obesity in children under 5 years [2].

Several modifiable factors during the first thousand days (from conception to two years of age) are associated with obesity risk later in life including excess pre-pregnancy weight [3], excessive weight gain during pregnancy [4–6], infant sleep deprivation [7], formula feeding [8, 9], high infant protein intake [10] and lower duration of exclusive breastfeeding (EBF) [11]. The WHO recommends EBF until six months of age and breastfeeding with adequate complementary feeding up to 2 years of age or more [12–14]. However, the role of breastfeeding in obesity prevention remains controversial. Some studies have reported a lower risk of obesity in breastfed versus formula fed children at 42 months (AOR 0.78; 95% CI 0.7–0.85) [15], at school age (AOR = 0.75; 95% CI 0.57–0.98) [16] and during adolescence (OR = 3.37), after adjusting for sociodemographic factors and parental obesity [17]. In contrast, other studies have shown that an intervention to promote breastfeeding was not associated with infant BMI or triceps skinfold thickness at 6.5 years [18]; and the risk of overweight at 4 years [19] and 11 years was not related to total or predominant breastfeeding duration [20]. EBF during the first three months postpartum could improve maternal weight loss. Comparisons between breastfeeding versus formula feeding women showed a significant time-effect of breastfeeding on maternal weight loss between 2 and 24 months postpartum, with a mean 2 kg greater weight loss in breastfeeding mothers [21].

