#### Primary outcomes and variables

Outcomes will be measured at birth (baseline) and 1, 3 and 4 months postpartum in the intervention and control groups. The primary outcomes are:
i)Prevalence of breastfeeding and EBF, ascertained by asking the mother about infant feeding practices during the last 24 h;ii)Growth velocity from birth, defined as change in weight for length in g/cm and length for age in cm/days;iii)Maternal weight loss after delivery in kg, using maternal weight at 24 h as baseline.

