### Sample size

The sample size was calculated to detect a difference in the prevalence of EBF between the intervention and control group of 23%, based on literature [43] reporting a baseline EBF of 22.8% in the control group (the prevalence of EBF for the Colombian population at 4 months in urban areas in 2010 [55]; there is a lack of data on EBF prevalence in overweight women in Colombia), with a power of 95%, an alpha error of 5% and a two-tailed calculation determined using the EpiInfo StatCalc program [56]. Assuming follow-up losses of 20%, 290 woman-child dyads are required, 145 in each group.

A convenience subsample of 60 women will be recruited, 30 from each group (20% of overall sample) for analysis of serum and milk prolactin concentration and macronutrient content.

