#### Measures

Questionnaires and assessments will be used to collect information among intervention and control groups at specific time-points, as shown in Table 1.
Maternal socioeconomic and demographic information, pregnancy information and paternal information: Information about residency, age, marital status, occupation, socioeconomic level, family size, family income, educational level, maternity leave, access to public services, social security, health benefits, smoking, alcohol consumption, family and medical history will be recorded. Gestational age will be determined by the date of the last menstruation, corroborated by sonographic studies available in the clinical notes. Paternal information will be reported by the woman and will include health status and monthly income.Intention to breastfeed: The scale uses five simple questions to determine the method of feeding that the woman plans for the baby. The scale has been validated and translated in previous studies [60].Maternal anthropometry: Anthropometric data - weight, height and mid upper arm circumference (MUAC) - will be collected in the last month of pregnancy, 24 h postpartum, and 1, 3 and 4 h months postpartum in minimal clothes. Weight will be measured in duplicate using an electronic scale (SECA 813, capacity 200 kg, precision 100 g), height measured in triplicate using a portable stadiometer (SECA 213, up to 205 cm) and MUAC measured in triplicate to the nearest cm (SECA 203 measuring tape, range 0 to 205 cm, graduation 1 mm). Weight gain during gestation (self-reported weight at the end of gestation minus pre-gestational weight) will be used as a baseline characteristic and as a covariate to predict the main outcomes.Breast examination: Participants will complete a questionnaire using illustrations of breasts to identify possible anatomical aspects that could make breastfeeding difficult (e.g. large breasts, flat nipples). This information will be used to focus the intervention for individual mothers.Edinburgh Postnatal Depression Scale (EPDS): This consists of 10 questions about feelings during the last week. It will be administered during the last month of gestation and 1 month postpartum as a tool to determine the risk of postpartum depression [54].Counselling register and evaluation: To assess the content of and adherence to the new EBF counselling intervention, a record of the problems identified will be kept during each visit. A questionnaire will also be administered by an independent investigator blinded to group allocation at the end of the study period (four months postpartum) which will include information on the problems identified, solutions and success, measured as: not successful (no problem resolution); limited success (partial resolution of the problem), or successful (problem solved).IPAQ short version: Physical activity questionnaire which considers types of physical activity, time (minutes per day) and number of days per week, and number of hours per day that the woman remains seated [61].Maternal food consumption: Determined using a standard food frequency questionnaire used and adapted in Colombian populations in other studies, and two multiple steps 24-h recall questionnaires to determine food consumption and nutrient intake including supplements, vitamins, minerals and maternal feeding problems; to be used as a baseline descriptive characteristic and as a potential confounder. This methodology is based on that described by the United States Department of Agriculture [58, 59]. To improve the quality of the data, photographs will be used to determine portion size [70]. Data analysis will be conducted using Colombian food composition tables [71], USDA standard nutrient reference database and food labels.Delivery information: Data about the type of delivery, newborn APGAR score, time of breastfeedng initiation, maternal-infant complications including those which delay the initiation of breastfeeding, and drugs administered during labour and the first 4 months after delivery.Newborn and infant anthropometry: Anthropometric variables - weight, length, MUAC and head circumference - will be measured by a trained nutritionist and dietitian following WHO protocol [72] at birth and 1, 3 and 4 months postpartum. Infant weight will be measured in duplicate using an electronic baby scale (TANITA 1583 with precision of 10 g, capacity 200 kg), length measured in triplicate using an infantometer (SECA 417, folding mechanism and foot stop, measuring range up to 100 cm), and head circumference and MUAC measured using a pediatric tape measure (SECA 201, range 0 to 205 cm, graduation 1 mm). Infant growth velocity will be defined as the change in the Z-score of weight for length, length for age, head circumference for age and mid upper arm circumference for age from birth to four months according to WHO growth standards [73]. Data collection will be performed by the same researcher in both groups to control information bias among observers.Breastfeeding information: This questionnaire collects information about initiation of breastfeeding at the hospital.Infant 24-h dietary recall: To determine the EBF prevalence, an infant 24-h recall will be used asking mothers about the foods consumed by the child during the previous day and infant feeding practices at 1, 3 and 4 months. = The counsellor will ask about the initiation, frequency and mode of preparation of specific beverages and semisolid foods or supplements since the last visit. This methodology will allow breastfeeding to be classified as exclusive or predominant according to WHO definitions [12].Breast-latching observation: Considers information about position of breastfeeding and maternal-infant perception of comfort during breastfeeding. This is a check-list that the investigator completes after watching a breastfeed [74].Breast milk macronutrients: Expression of breast milk (fore milk) will be performed at 1 and 4 months postpartum at the researcher’s office in the morning, using a Philips Single Electric Breast Pump under researcher supervision. The sample will be stored at − 20 °C in the laboratory at the Pontificia Universidad Javeriana for analysis. Content of macronutrients (carbohydrate, protein and fat) and energy in breast milk will be determined using the MIRIS Human Milk Analyzer, which uses infrared transmission spectroscopy and requires a human milk sample of 5 ml. Results will be recorded in the database.Breast milk prolactin: Determination of breast milk prolactin concentration will be performed using an Abcam ab226901 Human Prolactin SimpleStep ELISA kit. The procedure requires 2 ml of breast milk.Serum prolactin: To determine the maternal serum prolactin concentration, a non-probabilistic convenience subsample of 60 (20%) women will be selected. The blood sample will be taken at the laboratory of the institution, within 2 h of waking in the morning and before any food is consumed. The procedure will require 5 ml of maternal blood, which will be analyzed by ELISA (Abcam ab226901).

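### Three unranked primary outcomes, but the sample size covers exclusive breastfeeding alone at the full two-sided 5%, with no ranking, alpha split or success rule

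*Protocol article*

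**What the plan says.** The abstract lists the primary outcomes side by side: "The primary outcomes will be exclusive breastfeeding prevalence, infant growth velocity and maternal weight loss from birth up to 4 months after delivery". The section Primary hypotheses sets out three separate hypotheses to match, also unranked.

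The section Primary outcomes and variables expands them into five variables:

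- Any breastfeeding and EBF: "Prevalence of breastfeeding and EBF, ascertained by asking the mother about infant feeding practices during the last 24 h".
- Two growth velocities: "Growth velocity from birth, defined as change in weight for length in g/cm and length for age in cm/days".
- Maternal weight: "Maternal weight loss after delivery in kg, using maternal weight at 24 h as baseline".

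The same section gives the visits: "Outcomes will be measured at birth (baseline) and 1, 3 and 4 months postpartum in the intervention and control groups". Study design names 4 months after delivery as the primary end-point.

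Measures defines growth velocity a second way: "Infant growth velocity will be defined as the change in the Z-score of weight for length, length for age, head circumference for age", with mid-upper-arm circumference for age as a fourth component.

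Sample size uses one outcome only: EBF, 22.8% in the control group, a difference of 23 points, "with a power of 95%, an alpha error of 5% and a two-tailed calculation". With 20% losses this gives 290 dyads, 145 per group. The section gives no effect size, standard deviation or power for infant growth or maternal weight loss.

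Statistical analysis plans between-group comparisons of EBF prevalence, infant growth velocity and maternal weight loss on an intention-to-treat basis. It states no order of testing, no division of alpha and no rule for how many outcomes must succeed.

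**The concern.** The list of primary outcomes and the basis of the sample size are both protocol-level choices, and here they do not fit together. One part describes a trial with three equal primary questions. The other describes a trial with one question and all of the alpha spent on it.

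Which figure suffers depends on the success rule, and none is stated. If one significant outcome out of three is enough, the trial-level error rate exceeds 5%. If all three are needed, the error rate holds, but the 95% says little about the chance of success. If alpha is divided later, the 95% no longer applies to EBF at 290 dyads.

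At stake is how the result will be read. A chance finding on one variable could be reported as success on a primary outcome. A null on growth or maternal weight would be reported as a primary result although no one has shown what the trial could detect there.

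**Working it through.** **Inputs from the protocol article.** Control EBF 22.8%; difference 23 points, so 45.8% in the intervention arm; two-sided alpha 5%; power 95%; losses 20%; 145 per arm (Sample size). Three outcomes, five variables (Primary outcomes and variables). Primary end-point at 4 months (Study design).

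**Step 1: reproduce the 290.** Mean proportion (0.228 + 0.458)/2 = 0.343.

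n = [1.960 × √(2 × 0.343 × 0.657) + 1.645 × √(0.228 × 0.772 + 0.458 × 0.542)]² / 0.23² = 107.7, so 108 per arm.

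With continuity correction: (107.7/4) × [1 + √(1 + 4/(107.7 × 0.23))]² = 116.3, so 117 per arm. Dividing by 0.80 gives 147 per arm, 294 in total. That is within about 1.5% of the stated 290, so the EBF calculation is sound for one outcome at an unadjusted 5%.

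**Step 2: power for EBF at the planned size.** Evaluable dyads: 145 × 0.80 = 116 per arm. Power = Φ{[0.23√n − z × √(2 × 0.343 × 0.657)] / √(0.228 × 0.772 + 0.458 × 0.542)}. The continuity-corrected version replaces 0.23 by 0.23 − 1/n.

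| Alpha for EBF | z | Corrected | Uncorrected |
|---|---|---|---|
| 0.05 | 1.960 | 95.0% | 96.3% |
| 0.05/3 | 2.394 | 88.4% | 90.9% |

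Keeping 95% at 0.05/3 takes 145 evaluable per arm (corrected). 145/0.80 rounds up to 182 per arm, or 364 dyads.

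**Step 3: chance of at least one false positive at 4 months.** This takes each test at 5%, any one counting as success, and no true effects. Under independence it is 1 − 0.95^k. The correlated figures come from simulating normal test statistics with a common correlation; the correlations are assumptions.

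| Tests | Independent | Correlation 0.3 | Correlation 0.8 |
|---|---|---|---|
| 3 outcomes | 14.3% | 13.6% | 9.8% |
| 5 variables | 22.6% | 20.9% | 12.7% |

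If the four Z-score changes in Measures replaced the two growth velocities, there would be seven variables and 1 − 0.95⁷ = 30.2% under independence.

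**Step 4: if all three outcomes must succeed.** Alpha does not inflate. Even if each outcome had 95% power, joint power under independence would be 0.95³ = 85.7%.

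**Step 5: what can be said on growth and maternal weight.** At 116 per arm and two-sided 5%, the difference detectable with 95% power is (1.960 + 1.645) × √(2/116) = 0.47 SD, or 0.53 SD at 0.05/3. For assumed standardised differences of 0.2, 0.3, 0.4 and 0.5, power at 5% is 33%, 63%, 86% and 97%. The document gives no standardised difference, so it does not say where in this range the trial lies.

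**The case against.** **Silence is not a statement.** The only alpha in the article belongs to the EBF sample size. Nothing says that the other outcomes will be tested at 5%, and an unseen analysis plan could add an adjustment. This stands in part: the error rates above are conditional on an any-one-outcome rule. But an analysis plan could not split alpha for free, because 290 was computed with the full 5% on EBF, and it could not supply a basis for power on outcomes the fixed sample was not sized for.

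**A reader might multiply outcomes by visits.** Five variables at three post-birth visits would suggest a far larger error rate. The document does not support that count. Study design fixes 4 months as the primary end-point, birth is the baseline, and the planned random effects model can take repeated visits in one analysis.

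**A reader might infer that the 95% power is wrong.** It is not. The article attaches it to EBF, and it reproduces.

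**A reader might infer that growth and maternal weight are bound to come out null.** The Background cites a study "with a mean 2 kg greater weight loss in breastfeeding mothers", and one could dilute that by the 23-point shift in EBF. But that contrast is between breastfeeding and formula-feeding women over 2 to 24 months postpartum. Women who do not breastfeed exclusively are not all formula feeders, the follow-up here ends at 4 months, and no standard deviation is given. For growth there is no effect figure to work from. Power for these outcomes is unstated; it is not shown to be negligible.

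**Independence is not credible.** EBF is a subset of any breastfeeding, so the tests are correlated. This stands, and is why ranges are given. All of them remain above 5%.

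**Conclusion.** The point holds at protocol level. Three unranked primary outcomes do not match a sample size that gives the full two-sided 5% to one of them, and nothing in the article settles the conflict.

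Its size depends on the missing rule. If any one outcome at 5% counts, the false-positive chance at 4 months is about 10-14% for three outcomes and about 13-23% for five variables, for assumed correlations from 0.8 down to zero. If alpha is split three ways, EBF power falls from 95% to about 88% (corrected) or 91% (uncorrected), so the trial remains reasonably powered on EBF. If all outcomes must succeed, the 95% does not describe the chance of success.

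The EBF calculation itself is correct. Power for infant growth and maternal weight loss rests on effect sizes and standard deviations that the article does not give.

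**What to change.** **Preferred.** By a declared protocol and registry amendment, name EBF at 4 months as the single primary outcome at two-sided 5%. This is what the 290 dyads were sized for, so the 95% stands. Make any breastfeeding, infant growth velocity (under one stated definition) and maternal weight loss key secondary outcomes, tested in a fixed order and only if EBF is significant. Report the earlier visits as supportive estimates with confidence intervals.

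**Alternative.** Keep three primary outcomes, with one variable named for each. State that success on any one counts, and test them by Holm. State that EBF power at 116 evaluable per arm is at worst about 88% (continuity-corrected; 91% uncorrected), the figure at the first Holm step. It is higher if another outcome has already been rejected. Give the assumed effect and standard deviation for growth and maternal weight, or say that the trial was not sized for them.

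**Cost.** Neither route needs new data or more participants, unless 95% EBF power is to be kept under a three-way split (about 364 dyads). Under the first, infant growth and maternal weight loss lose the primary label; under the second, the stated EBF power becomes less favourable. The trial is already registered and ethically approved, so a change of primary outcomes must be dated and explained openly, and the registered outcomes amended to match. It should be made before any comparison of outcomes by arm has been seen.

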**Discussion:**

We hypothesize that the intervention will result in an increase in the initiation and maintenance of exclusive breastfeeding, allowing adequate infant growth velocity and maternal weight loss after delivery. It is hoped that the results of this trial will provide evidence to support public health policy on supporting breastfeeding in this vulnerable group of women.

**Trial registration:**

(UTN) **U1111–1228-9913** February 20th 2019; ISRCTN15922904

February 27th 2019, retrospectively registered.

## Background

In 2016, the World Health Organization (WHO) reported a worldwide prevalence of overweight (body mass index [BMI] higher than 25 kg/m^2^) and obesity (BMI > 30 kg/m^2^) of 40 and 15% respectively in women aged ≥18 years, with a global projection of 70 million overweight children aged under five years by 2025 [1], perpetuating the intergenerational transmission of obesity. In Colombia in 2015, the Instituto Colombiano de Bienestar Familiar (ICBF) reported a prevalence of overweight in the adult population of 37%, of which 22% were obese woman, and a prevalence of 6.3% of obesity in children under 5 years [2].

Several modifiable factors during the first thousand days (from conception to two years of age) are associated with obesity risk later in life including excess pre-pregnancy weight [3], excessive weight gain during pregnancy [4–6], infant sleep deprivation [7], formula feeding [8, 9], high infant protein intake [10] and lower duration of exclusive breastfeeding (EBF) [11]. The WHO recommends EBF until six months of age and breastfeeding with adequate complementary feeding up to 2 years of age or more [12–14]. However, the role of breastfeeding in obesity prevention remains controversial. Some studies have reported a lower risk of obesity in breastfed versus formula fed children at 42 months (AOR 0.78; 95% CI 0.7–0.85) [15], at school age (AOR = 0.75; 95% CI 0.57–0.98) [16] and during adolescence (OR = 3.37), after adjusting for sociodemographic factors and parental obesity [17]. In contrast, other studies have shown that an intervention to promote breastfeeding was not associated with infant BMI or triceps skinfold thickness at 6.5 years [18]; and the risk of overweight at 4 years [19] and 11 years was not related to total or predominant breastfeeding duration [20]. EBF during the first three months postpartum could improve maternal weight loss. Comparisons between breastfeeding versus formula feeding women showed a significant time-effect of breastfeeding on maternal weight loss between 2 and 24 months postpartum, with a mean 2 kg greater weight loss in breastfeeding mothers [21].

Despite the associated health benefits, only 43% of infants are exclusively breastfed during the first 6 months worldwide, and in 2015 this percentage was 36% in Colombia [22]. Breastfeeding initiation and duration are even lower in overweight women; those with pre-pregnancy BMI ≥ 30 kg/m^2^ are less likely to intend to exclusively breastfeed compared with normal weight and overweight women (78.8% vs 95.5 and 96.2%, respectively) [23]; whilst overweight women have significantly lower initiation and duration of breastfeeding than women in the normal range [24].

Low EBF and breastfeeding rates in overweight women [25] may be related to mechanical problems (congested mammary glands, larger amounts of adipose tissue, flattened areolas and oedema), delayed lactogenesis II as a consequence of inadequate suckling [26, 27], changes in prolactin levels [28], hypoplasia of the mammary gland and reduced stromal tissue [29]. Other risk factors are related to delayed early contact as a consequence of caesarean section [27] or a poor body image [30, 31]. Despite the reported lower rates of breastfeeding in obese mothers [30, there is some evidence that they are more likely to maintain EBF at 6 months than normal weight women if they are encouraged to exclusively breastfeed [32].

Interestingly, overweight women show lower serum prolactin and a lower prolactin response to suckling when compared with normal weight women at 48 h postpartum [26], which could explain the apparent delay of lactogenesis II and a shorter breastfeeding duration. Prolactin is involved in a variety of physiological processes in mammals [33] including the inhibition of lipogenesis [34] and an increase in glucokinase activity augmenting β cell secretion [35], resulting in an apparent inverse association between serum prolactin levels and metabolic syndrome and type 2 diabetes [36–38]. Prolactin in breast milk survives the infant gastrointestinal tract and is absorbed in the infant gut in a bioactive form or may act locally on the gut epithelium [39]; thus, maternal prolactin concentration could potentially influence infant fat and glucose metabolism during early lactation, both strongly related with obesity [40].

To date, only three experimental studies have been conducted using interventions that specifically aimed to prolong the duration of EBF until 6 months in obese mothers [41–43]. The strategies used included high intensity telephone support [43], peer counselling, breastfeeding education and anticipatory guidance [42], and low intensity telephone support with provision of a breast pump to facilitate lactation [41]. Only the intensive telephone intervention [43] resulted in prolonged EBF duration in obese mothers. The intervention had no effect on infant weight at 6 months and the EBF rate at 6 months remained lower than reported in the general Danish population [43]. It is possible that the support provided by telephone-based interventions is insufficient to improve breastfeeding practices in obese mothers. All studies were conducted in high-income countries, and no interventions have been developed or tested for low- or middle-income countries, including Colombia. Studies that aim to prolong breastfeeding and EBF in obese mothers should consider approaches that address the time-specific problems and the particular needs that these mothers face.

Since the middle of the twentieth century, counselling, defined as a “purposeful, private conversation arising from the intention of one person (couple or family) to reflect on and resolve a problem in their life, and the willingness of another person to assist in that endeavour” [44] has become one of the most widely used strategies for achieving health goals. It has been based on a wide variety of theoretical models and approaches, including the psychodynamic-interpersonal model [45], the cognitive-behavioural approach [46] and the person-centred approach [47]. In normal weight women, breastfeeding support based on counselling [48] by telephone, person to person, peer counselling and health care institution support strategies [49–51] have been shown to be effective for improving breastfeeding initiation, duration and exclusivity [52]. However, there is a lack of evidence regarding breastfeeding counselling specifically designed for overweight or obese women. Carl Rogers’ Client-Centred Theory allows the mother to take positive decisions towards a longer duration of breastfeeding and EBF as it enables the mother to recognize her strengths and limitations and those of her surroundings. Another important aspect of this theory is that it can be adapted to be used at critical time-points and to address specific problems faced by overweight mothers.

Considering the intergenerational transmission of obesity, the window of opportunity during the first thousand days, the positive effect of EBF counselling in normal weight women and the lack of evidence supporting an effective intervention to improve breastfeeding and EBF in overweight women, the purpose of this study is to evaluate the effects of a new approach to EBF counselling in overweight women, based on Carl Rogers´ Centred-Client Theory, on breastfeeding duration, infant growth velocity and maternal postpartum weight loss.

